**Figure 2 F2:**
[figure not shown]
Physical performance tests. **A **Chair stands test. **B **Walk test. **C **Functional reach. **D **Modified Romberg test.

#### Follow-up

At the first home visit the participants receive a fall calendar [16]. For the period of one year, the participants tick per week whether they did or did not fall during that week. A fall is defined as an unintentional change in position resulting in coming to rest at a lower level or on the ground [41]. Once per 3 months the participants return a calendar sheet by mail. When no sheet is received, or when the sheet is completed incorrectly, we inquire by telephone whether, and if yes, when the participant has fallen in the past 3 months.

The cost-evaluation questionnaire registers the costs made to prevent a new fall or the consequences of a new fall. The questionnaire assesses: the number of visits to physicians, therapists or day care centres; amount and aim of surgical procedures; number of days of admission to a hospital, home or nursing home; purchase of aids and adaptations in the home environment. The questionnaires are conducted 3, 6 and 12 months after the first home visit. The 3 and 6 months questionnaires are sent by mail and apply to the preceding 3 months. The 12 months questionnaire is assessed during the interview of the second home visit. This questionnaire applies to the preceding 6 months. When no questionnaire is received, or when it is completed incorrectly, the questionnaire will be completed by telephone.

During the second home visit, one year after the first visit, the same physical performance tests are conducted along with a reassessment of fall related healthcare costs, medical history, medication use, quality of life and activities of daily living. In addition, in the intervention group, adherence to the treatment regimen is evaluated. Treatment adherence in the intervention group is evaluated per recommendation given. Recommendations regarding changes in medication are evaluated by reassessing the medication use as described above. Adherence to all other recommendations (such as referrals to physical therapy or cardiologist) is assessed by asking whether, to what extent, and how the recommendations of the intervention were effected. The information from the participant is completed with information from the rapports of the involved specialists.

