### Procedure

All persons who consult the emergency department or primary care physician after a fall receive usual care. Within two weeks after the initial presentation, written information is sent and several days thereafter, the potential participants are contacted by telephone. All actual participants (who sign informed consent) are visited at their homes by a trained interviewer within 3 months after the fall incident. During the first home visit, the fall risk profile [16], fall history, independence in activities of daily living, quality of life and physical performance are measured. All high-risk participants will report falls during at least one year using a fall calendar and receive a cost-evaluation questionnaire at 3, 6 and 12 months after the first home visit. The times to first and second fall are the primary outcome measures. One year after the first home visit, they are visited a second time to reassess the activities of daily living, quality of life and physical performance. Scores on these questionnaires and tests are used as secondary outcome measures. Furthermore, the treatment adherence and medication use are evaluated. Table 1 presents an overview of the procedure and measurements. The measurements used are described later on in this article.

**Table 1 T1:** Overview of procedure and measurements

	Months	Measurements	Purpose
1st home visit	0	fall risk profile	selection high risk participants
		fall history	assessment of fall risk factors, confounders
		activities of daily living	secondary outcome measure
		quality of life	secondary outcome measure
		medication use	assessment of fall risk factors
		medical history	assessment of fall risk factors, confounders
		physical performance	secondary outcome measure
1st follow-up	3	1st calendar sheet	primary outcome measure
		3 months cost-evaluation	primary outcome measure
2nd follow-up	6	2nd calendar sheet	primary outcome measure
		6 months cost-evaluation	primary outcome measure
3rd follow-up	9	3rd calendar sheet	primary outcome measure
2nd home visit	12	activities of daily living	secondary outcome measure
		quality of life	secondary outcome measure
		medication use	treatment adherence
		medical history	secondary outcome measure, confounders
		physical performance	secondary outcome measure
		treatment adherence	confounder, to enhance the interpretation of the results
4th follow-up	12	4th calendar sheet	primary outcome measure
		12 months cost-evaluation	primary outcome measure

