### Measurements

#### Baseline assessment

During the first home visit, the risk of recurrent falling, fall history, medical history, medication use, independence in activities of daily living and quality of life are assessed. Risk of falling is assessed using a fall risk profile [16]. This profile, which was developed and validated in the Longitudinal Aging Study Amsterdam, [16] is used to screen participants with a high risk of recurrent falling. Recurrent falling is defined as 2 or more falls in a 6-month period [8,16,18]. This profile consists of 5 questions, 2 measurements (handgrip strength and body weight) and 2 interaction items. To measure handgrip strength a digital strain-gauged dynamometer (Takei TKK 5401, Takei Scientific Instruments Co. Ltd., Tokyo, Japan) is used. To measure body weight, a calibrated balance beam scale is used. On each item, points are scored and the scores are summed (range 0–30). Table 2 presents the diagnostic values of the risk profile for different cut off points on the fall risk score for 426 participants in the LASA-study who reported at least one fall in the previous year [16]. For this study, participants are defined at high risk of recurrent falling as the total score is 8 or higher. For an optimal combination of sensitivity and specificity, a cut-off score of 11 should be used. However, with a cut-off score of 11, a low sensitivity is obtained and too many participants with a high risk of recurrent falling will be missed. To ensure that not too many low risk participants are falsely diagnosed as high risk, the specificity should not be too low. At a cut-off score of 8, the sensitivity is higher than 50% and the specificity is higher than 70%.

**Table 2 T2:** Diagnostic values of the risk profile at different cut-off points in the total risk score

Cut-off in the total risk score	% at high risk group	Sensitivity (%)	Specificity (%)	Σ^a ^(%)	PV+ (%)	PV-	P_falls_
0 vs. ≥ 1	782	95.1	11.7	106.8	41.1	78.8	0.10 vs. 0.34
0–1 vs. ≥ 2	69.7	86.1	22.1	108.2	41.8	71.0	0.11 vs. 0.36
0–2 vs. ≥ 3	61.5	79.9	33.8	113.7	43.9	72.1	0.13 vs. 0.39
0–3 vs. ≥ 4	51.4	70.8	47.3	118.1	46.6	71.4	0.14 vs. 0.43
0–4 vs. ≥ 5	46.0	66.0	54.5	120.5	48.5	71.2	0.15 vs. 0.46
0–5 vs. ≥ 6	39.2	60.4	64.0	124.4	52.1	71.4	0.17 vs. 0.50
0–6 vs. ≥ 7	35.4	55.6	68.0	123.6	53.0	70.2	0.17 vs. 0.52
0–7 vs. ≥ 8	32.6	52.1	71.2	123.3	54.0	69.6	0.18 vs. 0.54
0–8 vs. ≥ 9	29.8	48.6	74.3	122.9	55.1	69.0	0.19 vs. 0.56

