### Statistics

Data will be primarily analysed according to the intention-to-treat principle, i.e., including all randomized participants, regardless of whether they received or did not receive the intervention. Subsequently, the results of the intention-to-treat analysis will be compared with the results of an on-treatment analysis.

At baseline, differences in baseline characteristics will be compared between the intervention and control group to examine comparability between the two groups.

To examine the effectiveness of the multidisciplinary transmural care, Cox proportional hazards regression will be conducted, with time to first fall and time to second fall within one year of follow-up as outcome measures, and with age, gender and living situation as covariables. Subsequently, multiple linear regression analyses will be used to compare differences in secondary outcome measures (ADL-score, QoL, physical performance and morbidity data) at 12 months follow-up between intervention and control group.

The economic evaluation will be conducted from a societal perspective, which implies that all costs and outcomes are taken into account. The economic evaluation will involve calculating cost-effectiveness and cost-utility ratios. The incremental costs and effects of the intervention will be compared with usual care. The difference in costs of the intervention group and usual care group will be computed using bootstrapping techniques. Uncertainty ratios will be presented on cost effectiveness and cost utility planes. Acceptability curves will also be estimated. These present the probability that the intervention is cost-effective given a ceiling ratio that policy makers are willing to invest.

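### The weekly yes/no fall calendar cannot show a second fall in the same week as the first, so the primary outcome time to second fall is slightly mismeasured (minor)

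*Protocol article*

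**What the plan says.** The Follow-up section describes the instrument: for one year, "the participants tick per week whether they did or did not fall during that week". The recording is checked only by exception: "When no sheet is received, or when the sheet is completed incorrectly, we inquire by telephone whether, and if yes, when the participant has fallen". A correctly completed sheet prompts no call, and the enquiry as described asks whether and when, not how many times.

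The Procedure section states: "The times to first and second fall are the primary outcome measures". The Statistics section plans Cox regression with "time to first fall and time to second fall within one year of follow-up as outcome measures". The Baseline assessment section also thinks in numbers of falls: "Recurrent falling is defined as 2 or more falls in a 6-month period".

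No section gives a rule for several falls in one week, and none plans an analysis of fall counts or rates.

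**The concern.** The endpoint is an ordinal event, the second fall. The instrument records a weekly indicator. The two agree unless the first two falls share a calendar week. In that case the sheet shows one tick, and the participant's second fall is dated to the next ticked week or censored at one year. An analysis plan cannot repair this later, because the information was never collected.

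At stake are the accuracy of one of the two primary outcomes and the completeness of the fall count. What needs checking is how often this happens, and whether it changes the comparison between the groups.

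**Working it through.** **1. The plan's own figure.** The Study population section needs 57 per group, or 82 after 30% drop-out: 57/(1 − 0.30) = 81.4, rounded up to 82. This reproduces. The 57 rests on a 50% difference in fall incidence with no control value stated. Assuming proportions of 50% and 25%, two-sided 0.05 and 80% power:

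n = [1.960·√(2·0.375·0.625) + 0.842·√(0.5·0.5 + 0.25·0.75)]² / 0.25² = (1.342 + 0.557)² / 0.0625 ≈ 57.7, so 58.

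This is close to the stated 57. The weekly tick does not change the sample size.

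**2. Inputs for the size of the problem.** The recording unit (one tick per week) and one year of follow-up come from the article. The fall rate and its variation between persons are not given. Assumed: mean 1.2 to 3 falls per year, gamma-distributed personal rates with shape 0.5 to 2, and falls independent in time given the personal rate.

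**3. Formulas for a person with rate λ per year, μ = λ/52.**

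- Second fall within the year: P₂ = 1 − e^(−λ)(1 + λ)
- First two falls in the same week: S = [1 − e^(−μ)(1 + μ)]·(1 − e^(−λ))/(1 − e^(−μ))
- Same week and no later ticked week: N = 52·[1 − e^(−μ)(1 + μ)]·e^(−51μ)
- Share of the fall count lost: 1 − 52(1 − e^(−μ))/λ

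**4. Worked example, λ = 2 for everyone.** μ = 0.03846 and P₂ = 0.5940.

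- S = 0.000721 × 0.8647/0.03773 = 0.01652, so 0.01652/0.5940 = 2.8% of second-fallers are affected.
- N = 52 × 0.000721 × 0.1406 = 0.00527, so 0.00527/0.5940 = 0.9% are never registered. The other 1.9% are dated late.
- Count lost: 1 − 0.03773/0.03846 = 1.9%.

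Simulation gives the same values, with a mean delay of about 14 weeks among those dated late.

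**5. Averaging over gamma-distributed rates.** S, N and P₂ are each averaged before dividing. For mean m and shape a, the count lost is 1 − (52/m)·[1 − (1 + m/(52a))^(−a)].

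| Mean per year | Shape | Same week, % of second-fallers | Never registered, % | Count lost, % |
|---|---|---|---|---|
| 1.2 | 2 | 2.7 | 1.0 | 1.7 |
| 1.2 | 0.5 | 3.6 | 0.7 | 3.3 |
| 2 | 1 | 3.8 | 0.7 | 3.7 |
| 3 | 2 | 4.1 | 0.5 | 4.2 |
| 3 | 0.5 | 5.8 | 0.4 | 7.9 |

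**6. Effect on the treatment comparison.** With the fall rate halved by the intervention, the second-fall rate ratio was simulated with exact dates and with weekly ticks. At 2 falls per year in the control group it was 0.361 and 0.361 (no variation between persons), 0.485 and 0.485 (gamma shape 1), and 0.548 and 0.547 (gamma shape 0.5). Over control rates of 1 to 4 per year the largest shift was 0.002 (0.423 to 0.425). The largest power loss by the Schoenfeld formula was about 0.4 percentage points (64.8% to 64.4%). Simulated Cox power for second fall in three scenarios was 70% and 68%, 82% and 82%, and 51% and 52%.

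**7. Counting falls or counting ticked weeks.** Simulated power of negative binomial regression on all falls and on weeks with a fall was 83% and 83%, 95% and 94%, and 82% and 79%. At 1.2 falls per year, 85 per arm and the rate halved, the 83% compares with 65% for Cox on first fall and 70% for Cox on second fall.

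**The case against.** The strongest reply is that the consequence is tiny: hardly any second-fallers are lost, and the comparison between groups does not move. That stands, and it sets the severity.

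Three stronger readings are tempting, and the document does not support them.

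- **Bias toward no difference.** A reader might infer that losing more second falls in the arm that falls more pulls the effect toward the null. Step 6 shows no shift of any practical size.
- **Falls cannot be counted, or a count analysis is blocked.** Ticked weeks can be counted and modelled with little loss (step 7). Nor does the article define fall incidence as falls per person-year. The 57 is nearly reproduced by proportions of fallers, which need only whether a person fell.
- **The power gap between Cox and negative binomial measures the harm of the tick.** It does not. It comes from using all falls instead of the first one or two. Stopping at the second fall follows from the chosen outcomes and is not an error.

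It can also be said that the article is a condensed account that cites an earlier study for the calendar, and that the sheet itself is not shown. A date or number field may exist. The point therefore concerns the instrument as described. But the article does describe what participants record and what the telephone call asks, and neither yields a second fall within a week.

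**Conclusion.** The point holds as a minor mismatch between instrument and endpoint. The range of about 3% to 6% of second falls affected rests on assumed rates, because the article states none. It also rests on falls being independent within a person. If falls cluster, for example if 10% of falls are followed by another within a week (a further assumption), about 11% of second-fallers would have both falls in one calendar week, and the count would be understated by 7% to 10%. The article offers no figure on clustering, so this shows sensitivity and is not an expected value.

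The reason to act is that the missing information is unrecoverable and cheap to collect. It is not that the trial's conclusion is threatened.

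**What to change.** 1. On the remaining calendar sheets, add the number of falls and the date of each fall for any ticked week. The Progress of the study section has follow-up running to July 2008, so later sheets can still change.
2. Have the existing telephone enquiry also ask for the number and dates of falls.
3. Define time to second fall from these dates. For sheets already returned, state how a single ticked week is handled, for instance as one fall in that week.
4. Separately, and as an improvement only, prespecify a supporting negative binomial regression of all recorded falls with log follow-up time as offset. Where only ticks exist, it can be run on weeks with a fall.

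The cost is a reprinted sheet, an added question in calls already made, and slightly more effort for participants. The data will mix weekly and dated records, which the definition in item 3 must cover. The sample size and the two planned Cox models stay as they are.

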### Statistics

Data will be primarily analysed according to the intention-to-treat principle, i.e., including all randomized participants, regardless of whether they received or did not receive the intervention. Subsequently, the results of the intention-to-treat analysis will be compared with the results of an on-treatment analysis.

At baseline, differences in baseline characteristics will be compared between the intervention and control group to examine comparability between the two groups.

To examine the effectiveness of the multidisciplinary transmural care, Cox proportional hazards regression will be conducted, with time to first fall and time to second fall within one year of follow-up as outcome measures, and with age, gender and living situation as covariables. Subsequently, multiple linear regression analyses will be used to compare differences in secondary outcome measures (ADL-score, QoL, physical performance and morbidity data) at 12 months follow-up between intervention and control group.

The economic evaluation will be conducted from a societal perspective, which implies that all costs and outcomes are taken into account. The economic evaluation will involve calculating cost-effectiveness and cost-utility ratios. The incremental costs and effects of the intervention will be compared with usual care. The difference in costs of the intervention group and usual care group will be computed using bootstrapping techniques. Uncertainty ratios will be presented on cost effectiveness and cost utility planes. Acceptability curves will also be estimated. These present the probability that the intervention is cost-effective given a ceiling ratio that policy makers are willing to invest.

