### Study population

The study population consists of persons of 65 years and over, who consult the Accidents and Emergency Department of the VU University Medical Center (Amsterdam, The Netherlands) or their primary care physician between April 2005 and April 2007 after a fall incident. Inclusion criteria are living independently or in a residential home, living in the vicinity of the VU University Medical Center and having experienced a fall. Exclusion criteria are inability to sign informed consent, inability to provide a fall history, fall due to a traffic or occupational accident, living in a nursing home and acute pathology requiring long-term rehabilitation, such as a stroke.

200 high-risk participants will be included in the intervention study, of which we will enrol 100 participants in the intervention group and 100 in the control group. With a significance level of 0.05, a power of 80% and an expected difference in fall incidence of 50% [13] between the intervention and control group, 57 participants are needed both in the intervention and in the control group. Taking into account a drop-out rate of 30% a minimum of 82 participants are needed in each group. With 100 persons in both the intervention and control group, the numbers are certainly high enough to detect statistical significant differences.

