Fall history is assessed with the fall history instrument (Carefall Triage Instrument, version 007), which is a questionnaire developed by the Academic Medical Center, the VU University Medical Center and the Erasmus Medical Center, The Netherlands. The fall history collects data on the circumstances of the last and previous falls, mobility and risk factors of bone loss and osteoporosis, social status and general health. Medical history is assessed using a questionnaire on self-reported (chronic) diseases both in the past and present. The questionnaire includes 7 major chronic diseases, i.e. chronic lung diseases, cardiac diseases, vascular diseases, stroke, diabetes mellitus, malignant neoplasms and joint disorders (i.e. osteoarthritis and rheumatoid arthritis). In addition, participants are asked to indicate any other chronic disease, including psychological diseases, which they have or have had. Medication use is assessed by directly copying the names of drugs used in the previous two weeks from the containers. The name, doses per unit, number of times taken per day, time of administration, doses per intake, purpose, prescription or over the counter (OTC) and whether the drug has been prescribed after the fall are assessed for each drug. This information is compared to medication records of the public pharmacy. Level of independence in activities of daily living (ADL) will be examined using the Barthel Index (range 0, fully dependent, to 20, fully independent) [33]. The level of functioning on more complex daily activities will be examined using a scale of instrumental ADL introduced by Lawton and Brody (range 0, fully dependent, to 8, fully independent) [34]. Quality of Life (QoL) is examined using the Dutch translations of the SF-12 and the EQ-5D. The SF-12 consists of 12 items and is a abbreviated version of the SF-36 [35]. The SF-12 has been designed and validated to measure health related QoL in large population studies [35,36]. The EQ-5D (EuroQol) has been developed to generate a general index of experienced health and for the assessment of Quality Adjusted Life Years (QALY). It is therefore suitable for economic evaluations [37]. The assessment consists of 5 items (mobility, self-care, usual activities, pain/discomfort and anxiety/depression) and a visual analogue scale (0, worst, to 100, best imaginable health state) [37]. The fall history, ADL and QoL questionnaires are sent to the participants prior to the first home visit. Participants are asked to complete these questionnaires before the home visit. The visiting researcher assists participants who are unable to complete these questionnaires independently.

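### The primary Cox models leave out the baseline fall risk score, which is already collected and remains strongly prognostic at scores of 8 and above: a modest loss of efficiency, not a bias

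*Protocol article*

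**What the plan says.** The Statistics section names Cox regression "with time to first fall and time to second fall within one year of follow-up as outcome measures" and states the adjustment set: "and with age, gender and living situation as covariables". No other covariate is named for the primary models.

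The Procedure section has the fall risk profile and the fall history measured at the first home visit. The score runs from 0 to 30 and a total of 8 or more qualifies a person for the trial. Under Study design and randomisation, residents of a residential home enter the high-risk group directly, so some of them may score below 8.

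Table 1 gives the risk profile one purpose, the selection of high-risk participants. It gives fall history two, one of which is confounding. On its content, the Baseline assessment section says: "The fall history collects data on the circumstances of the last and previous falls".

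**The concern.** The trial measures a score that was built to predict recurrent falling, uses it to decide who enters, and then leaves it out of the analysis of falls. If the score still separates participants by risk after entry, a Cox model without it gives a hazard ratio somewhat closer to 1 and has less power for both primary outcomes. It also leaves a chance imbalance in the score uncorrected. The randomisation described uses blocks of four, and no stratification by score is mentioned.

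The article states the covariate list itself, so this is not a detail left to an analysis plan that is not shown. Fall history raises a smaller matter: Table 1 gives it a role that the model does not follow.

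**Working it through.** **1. The plan's own figure.** The article states that "57 participants are needed both in the intervention and in the control group" and then "Taking into account a drop-out rate of 30% a minimum of 82 participants are needed in each group". The control incidence is not given and has to be assumed. For two proportions (pooled variance, two-sided 0.05, 80% power, halved incidence), 0.50 vs 0.25 gives 58 per arm and 0.505 vs 0.2525 gives 57. Drop-out: 57 / (1 − 0.30) = 81.4, rounded up to 82. The figure is therefore reproduced if about half the controls fall; an incidence of 0.40 would give 82 and 0.60 would give 42 before drop-out. Nothing in it depends on covariate adjustment.

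**2. Is the score prognostic among those who qualify?** With 144 recurrent and 222 non-recurrent fallers, sensitivity × 144 and (1 − specificity) × 222 give whole-number counts that reproduce the sensitivity, specificity and both predictive values in every row of Table 2.

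| Score | Recurrent | Not recurrent | Total | Risk | Printed PV+ |
|---|---|---|---|---|---|
| ≥ 8 | 75 | 64 | 139 | 54.0% | 54.0% |
| ≥ 11 | 59 | 32 | 91 | 64.8% | 64.8% |
| ≥ 16 | 20 | 5 | 25 | 80.0% | 80.0% |

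Subtracting adjacent rows:

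- 8–10: (75 − 59) / (139 − 91) = 16/48 = 33%
- 11–15: (59 − 20) / (91 − 25) = 39/66 = 59%
- ≥ 16: 20/25 = 80%

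Two cautions apply. The counts sum to 366, while the column for the share at high risk divides by 426 (139/426 = 32.6%). The last column of Table 2 does not always agree with PV+ (0.91 against 64.8% at ≥ 11) and was not used for the bands.

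**3. What omitting it costs.** Trials were simulated with 100 per arm, as planned ("we will enrol 100 participants in the intervention group and 100 in the control group"). Score bands were drawn in proportions 48, 66 and 25 out of 139. Band-specific fall rates were set to give the risks above, 30% dropped out at uniform times, and follow-up was one year. There were 1,000 runs per setting. Table 2 does not state its risk window, so 12 and 6 months were both tried. Extra heterogeneity between persons was either absent or a gamma frailty with variance 0.5. Each trial was analysed by Cox regression with treatment alone and with treatment plus score bands.

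Power (%), without → with the score:

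| Window, frailty | Rate ratio | First fall | Second fall |
|---|---|---|---|
| 12 mo, none | 0.5 | 96.1 → 97.6 | 98.5 → 99.4 |
| 12 mo, 0.5 | 0.5 | 83.2 → 86.5 | 87.1 → 91.1 |
| 6 mo, none | 0.5 | 98.5 → 98.9 | 99.7 → 99.9 |
| 6 mo, 0.5 | 0.5 | 84.3 → 88.7 | 95.0 → 96.9 |
| 12 mo, none | 0.6 | 79.8 → 84.3 | 88.3 → 91.6 |
| 12 mo, 0.5 | 0.6 | 57.7 → 61.0 | 67.5 → 72.7 |
| 6 mo, none | 0.6 | 86.7 → 90.8 | 96.6 → 98.5 |
| 6 mo, 0.5 | 0.6 | 60.8 → 66.2 | 71.3 → 77.0 |
| 12 mo, none | 0.7 | 48.9 → 53.7 | 61.4 → 66.4 |
| 12 mo, 0.5 | 0.7 | 35.1 → 37.4 | 41.1 → 48.1 |
| 6 mo, none | 0.7 | 58.1 → 66.5 | 78.0 → 84.9 |
| 6 mo, 0.5 | 0.7 | 33.3 → 36.4 | 44.1 → 51.0 |

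Power is lower without the score in all 24 comparisons. The loss is 0.2 to 4.4 points at a rate ratio of 0.5 and 1.9 to 8.4 points at 0.6 and 0.7. The average hazard ratio moves slightly toward 1, for example 0.52 instead of 0.49 for first fall (12 months, no frailty, rate ratio 0.5). A single power near 80% has a simulation standard error of √(0.8 × 0.2 / 1000) = 1.3 points, so the smallest gains should not be read closely.

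**The case against.** The strongest reply is that this is a preference about efficiency. The listed covariates are prespecified baseline variables, randomisation makes the comparison valid without the score, and the type I error is unaffected. The shift in the hazard ratio is the usual gap between a marginal and a conditional estimate. All of this stands.

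The size is also open to challenge. The simulation set the score against no adjustment, whereas the plan adjusts for three variables. Living situation in particular may overlap with risk. That stands too, so the gains above may be larger than those attainable in practice.

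A reader might infer three stronger things that the article does not support:

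- That the score and fall history are the collected variables most related to the outcome. The article gives no prognostic strength for fall history, age, gender or living situation, so no ranking is possible.
- That the omission leaves the trial underpowered. Low power appears only at effects smaller than planned; at the planned effect it stays above 80% without the score.
- That Table 1 contradicts the model over the score. It gives the score a selection role only. The mismatch concerns fall history, and the confounder label is loose, since it is also attached to medical history and to treatment adherence, which arises after randomisation.

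The reply does not remove the main point: a prognostic baseline value already collected for entry is unused in a model whose covariates the article fixes.

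**Conclusion.** The point holds as a modest, avoidable loss of efficiency. It is neither an error nor a bias, and the stated sample size is not undermined. The loss matters more if the true effect is smaller than planned, a possibility the Background leaves open by citing multifactorial trials without effect.

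The conclusion rests on these assumptions: Table 2 risks carry over to this population; a 50% difference is read as a rate ratio of 0.5; and the risk window and frailty lie in the ranges tried. Residents scoring below 8 were not modelled and would widen the spread of the score. Using three bands ignores differences within a band. Fall history was not modelled because the article gives no figures for it, so its omission is a labelling mismatch with no size attached.

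**What to change.** Add to the Statistics section, before any analysis, that both Cox models include treatment group, age, gender, living situation and the baseline fall risk score as a continuous covariate. For residential-home entrants, use the score measured at the same visit. Confirm that it is recorded for all of them, because direct assignment to the high-risk group leaves this unclear.

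For fall history, choose one of two courses. Either name a specific baseline variable now, provided one is recorded in usable form, or change the Table 1 label to match the model. The article describes circumstances of earlier falls but does not state that a count is recorded. The items of the risk profile are not listed either, so check for overlap before entering both.

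The cost is a line or two of text. The score needs no new data, and according to the Progress section data analysis starts only after follow-up ends.
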